### Monitoring the intervention

During the 6-month intervention period, patients are required to use the EMPOWER-SUSTAIN self-management mobile app for a cumulative period of 2 h and be seen at least once by the PCPs for follow-up care. A separate web interface will be created for PCPs to monitor patients’ log-in frequency and duration of use of the tool. Patients who do not comply with the use and follow-up requirements will be considered as lost to follow-up. Patients who are lost to follow-up or who withdraw from the trial will not be replaced. Analysis will be by intention to treat (ITT). There is no other specific concomitant care and intervention that are permitted or prohibited during the trial.

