### Outcome measures

Outcome measures are divided into primary and secondary outcomes. These measures will be obtained from both intervention and control groups at baseline and 6 months after the delivery of the intervention.

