### Sample size determination

Sample size is calculated using Power and Sample Size Calculation software version 3.1.2 [84], based on the findings of a randomised controlled trial evaluating the effects of a web-based self-management intervention for adults with chronic conditions on patient activation scores, measured by the PAM-13 questionnaire [48]. In the intervention group, the mean patient activation score at baseline was 65.33, and the mean score after the intervention was 71.30 (mean difference, 5.97 ± 9.70; t57 = 4.683; *P* < 0.001) [48]. In the control group, the mean patient activation score at baseline was 66.89, and the mean score at the end of the study period was 68.93 (mean difference, 2.04 ± 10.01; t67 = 1.677; *P* = 0.10) [48]. Therefore, the mean difference between the two groups was 3.93.

Based on this assumption, a sample size of 97 patients per group is sufficient to detect mean difference of δ = 3.93 in the patient activation score between the two groups, with a standard deviation of σ = 9.70 using a two-tailed *t* test of difference between means with 80% power (power = 0.8), 5% level of significance (α = 0.05), and sample size ratio of 1:1 between the two groups (m = 1). After considering a drop-out rate of 20%, the sample size required is 116 patients per group, giving a total of 232 patients to be recruited for this study.

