### Data management

Each CRF will be given a unique identifier. Data collected using the CRF and all the questionnaires will be checked by a research assistant to ensure completeness. If any missing data are found, the patients will be contacted again via telephone. Double data entry into the IBM SPSS Statistics version 24 software (IBM, Armonk, NY, USA) will be conducted, and data cleaning will be done to manage outliers, missing values, and inconsistencies. The clean datasets for baseline and outcome will be used for analysis. Data will be stored in a secure database at the Institute of Pathology, Laboratory and Forensic Medicine (I-PPerForM), Universiti Teknologi MARA (UiTM).

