### Statistical analysis

The analysis will be conducted using IBM SPSS Statistics version 24 software.

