#### Effectiveness analysis

ITT analysis will be applied to measure the potential effectiveness of the EMPOWER-SUSTAIN Self-Management e-Health Intervention on the primary and secondary outcome measures based on the initial treatment assignment. Mixed model repeated measures analysis of variance will be carried out to evaluate the potential effectiveness (i.e., to compare the mean changes in patient activation, PA, diet, patients’ chronic illness care, and patient–physician interaction satisfaction scores) with regard to perceived absolute 10-year CVD risk within and between the intervention and control groups at baseline and 6-month follow-up.

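### The analysis is called ITT, but the named mixed model repeated measures ANOVA can be read two ways, and one reading leaves out about 46 of the 232 randomised patients

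*Protocol article*

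**What the plan says.** The Effectiveness analysis section of the protocol article makes two commitments. The first is the population: "ITT analysis will be applied to measure the potential effectiveness", with patients grouped "based on the initial treatment assignment". The second is the method: "Mixed model repeated measures analysis of variance will be carried out to evaluate the potential effectiveness". That sentence goes on to describe a comparison of mean changes, both inside each group and across groups, at the two assessments.

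Other sections bear on who ends up in the analysis:

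- Outcome measures fixes two time points: "These measures will be obtained from both intervention and control groups at baseline and 6 months after the delivery of the intervention".
- Sample size determination expects losses: "After considering a drop-out rate of 20%, the sample size required is 116 patients per group".
- Monitoring the intervention rules out making them good: "Patients who are lost to follow-up or who withdraw from the trial will not be replaced". It also repeats the ITT commitment.
- Data management says patients with missing data will be telephoned, and then that "data cleaning will be done to manage outliers, missing values, and inconsistencies".
- Statistical analysis names the software: "The analysis will be conducted using IBM SPSS Statistics version 24 software".

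No section says whether a patient without a 6-month score stays in the primary analysis.

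**The concern.** ITT is defined here only by arm, and the method label fits two different procedures. A between-within ANOVA (the repeated-measures routine of the general linear model) deletes any patient with an incomplete pair. There is only one post-baseline assessment, so every patient without a 6-month score goes. A likelihood-based linear mixed model uses whatever scores each patient has, so a baseline-only patient remains and informs the estimate. SPSS offers both routes.

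The choice therefore decides whether the result describes the randomised patients, under a stated assumption about the missing scores, or only those who stayed. The Study setting section says the pilot is meant to give safe assumptions about effect size for the definitive trial. If a complete-pairs estimate is passed on under an ITT label, the later trial's planners will not know that it depends on who dropped out. Unequal drop-out is plausible because only one arm is asked to use an app during the study.

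**Working it through.** **The plan's own figures.** With a difference of 3.93, SD 9.70, two-sided alpha 0.05 and 80% power, the t-test solution is 96.6 per group. This rounds up to the stated 97. Then 97 x 1.2 = 116.4, which gives the stated 116 per group and 232 in total.

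**Patients affected.** 0.20 x 232 = 46.4 would lack a 6-month score, about 23 per arm (0.20 x 116 = 23.2). About 186 would have both scores, or 93 per arm. The t-test power for 3.93 is then 78.5%, against 80.2% at 97 per arm. The loss of power is small; the main question is bias.

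**Bias of the complete-pairs change.** The correlation and the drop-out mechanism below are assumptions, since the article gives neither. Let r be the correlation between baseline and 6-month scores, with equal SDs at both times.

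- Score SD = 9.70 / sqrt(2(1 - r)).
- Let m be the mean baseline z-score among those who stay. Regression to the mean gives a bias in that arm's mean change of -(1 - r) x score SD x m = -9.70 x sqrt((1 - r)/2) x m.
- Drop-out is set at 20%, with a given odds ratio per SD of lower baseline score. Numerical integration gives m = 0.079, 0.129 and 0.186 for odds ratios 1.5, 2 and 3.

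| Odds ratio | r = 0.5 (factor 4.85) | r = 0.6 (factor 4.34) | r = 0.7 (factor 3.76) |
|---|---|---|---|
| 1.5 | -0.38 | -0.34 | -0.30 |
| 2 | -0.62 | -0.56 | -0.48 |
| 3 | -0.90 | -0.80 | -0.70 |

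If this happens in the intervention arm only, the between-arm difference is too small by the amount shown. That is about 8% (0.30/3.93) to 23% (0.90/3.93) of the planned effect. If the same mechanism acts equally in both arms, the biases cancel.

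**Comparison of the two readings by simulation.** There were 4,000 runs with 116 per arm and a true difference of 3.93. The mixed model was fitted by maximum likelihood to all available scores, with separate baseline means by arm.

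| Assumed drop-out | r | Complete pairs | Mixed model |
|---|---|---|---|
| Completely at random | 0.5 | 3.90 | 3.90 |
| Completely at random | 0.7 | 3.97 | 3.97 |
| Depends on low baseline, intervention arm only (odds ratio about 3.3 per SD) | 0.5 | 2.89 | 3.90 |
| Same | 0.7 | 3.11 | 3.90 |
| Depends on the unseen change, intervention arm only | 0.5 | 5.98 | 5.54 |
| Same | 0.7 | 5.95 | 5.69 |

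The second mechanism is slightly stronger than the top of the formula grid, so its bias is slightly larger. Under the third mechanism both methods are wrong, and in the same direction.

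**Precision.** The variance of a change score is proportional to 2(1 - r). With a common baseline mean, the 6-month comparison has variance proportional to 1 - r^2. The ratio is (1 + r)/2, which is 0.75 at r = 0.5 and 0.85 at r = 0.7.

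**The case against.** The strongest reply is that the article does say mixed model and nowhere says that incomplete pairs are excluded. The ITT commitment, made in two sections, favours the reading that keeps patients. This stands: the exclusion of about 46 patients is conditional on the between-within reading. A reader might infer that the primary result will certainly be a completers' effect, but the text does not settle that. The ANOVA reading is nevertheless the more natural one, because the sentence speaks of analysis of variance and of mean changes compared inside and across groups at two times.

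A second reply is that the choice of procedure and the handling of missing scores belong in a fuller protocol or analysis plan that is not shown. That would answer a complaint about absent detail. Here, however, the article itself names a population and a method that conflict on one reading and agree on the other, so any later plan must interpret or override this sentence.

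A third reply is that this is a pilot that will measure retention and review its own statistical methods. This lowers the stakes, but the effect size is one of the things it is meant to hand on.

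Finally, the bias range rests on assumed one-arm, baseline-dependent drop-out. This is also correct, and the range should be read only as an illustration.

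**Conclusion.** The point holds as an ambiguity with consequences. The named method fits two procedures that treat about 46 of 232 patients differently, and only one of them fits the ITT label. If drop-out is completely at random, the two give the same answer. If drop-out in the intervention arm alone depends on low baseline activation, the complete-pairs change is off by about -0.3 to -0.9 points against 3.93, given odds ratios of 1.5 to 3 per SD, correlations of 0.5 to 0.7 and 20% loss. The likelihood model removes that bias.

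A reader might go further and suppose that completers overstate the effect because drop-outs gain nothing. The documents give no information on how drop-outs fare. That scenario would also not measure this fault: if drop-out were otherwise unrelated to baseline, the mixed model would return the same figure as the complete pairs. It would also push the estimate up, whereas the baseline-dependent case pushes it down.

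The rule in Monitoring the intervention that counts low app users as lost to follow-up is a separate matter. It could, however, raise the number affected in the intervention arm.

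**What to change.** In Effectiveness analysis, replace the method label with a likelihood-based linear mixed model (the MIXED procedure in SPSS). State that it includes every randomised patient with a baseline or 6-month score, in the arm assigned. Fit a common baseline mean for the two arms, take the arm difference at 6 months as the effect, and state the missing-at-random assumption. This model is also more precise than the change-score ANOVA, with a variance ratio of 0.75 to 0.85 at the assumed correlations.

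The model does not protect against drop-out that depends on the unseen outcome, so add one sensitivity analysis for that case. For example, let missing intervention-arm outcomes follow the control-arm mean change. If the ANOVA on complete pairs is kept instead, call it a complete-case analysis.

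The cost is a few lines of text and one extra analysis, with no new data, patients or software. The small downside is that the primary estimate then rests openly on the missing-at-random assumption. The Trial status section reports that recruitment had not begun, so the change can be made before any outcome is seen.

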### Hypotheses

The primary hypothesis is that the mean score of patient activation would improve with the EMPOWER-SUSTAIN Self-Management e-Health Intervention. The secondary hypotheses are that WC, body mass index (BMI), BP, PA level, eating behaviour, patients’ perceptions and experiences of receiving care for chronic conditions, patient–physician satisfaction, and the accuracy of the CVD risk perception would improve with the EMPOWER-SUSTAIN Self-Management e-Health Intervention.

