### Primary outcome

The primary outcome will be measured by the mean change in patient activation score using the Patient Activation Measure short form–Malay version (PAM-13-M) questionnaire [24].

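### The two-time repeated-measures ANOVA is a change-score analysis: valid, but less precise than a baseline-adjusted comparison, sensitive to chance baseline imbalance, and listed alongside within-arm comparisons

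*Protocol article*

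**What the plan says.** All statements are in the protocol article.

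- **Model** (Effectiveness analysis): "Mixed model repeated measures analysis of variance will be carried out to evaluate the potential effectiveness". The stated aim is "to compare the mean changes in patient activation, PA, diet, patients’ chronic illness care, and patient–physician interaction satisfaction scores", and the comparisons are made "within and between the intervention and control groups at baseline and 6-month follow-up".
- **Measurement times** (Outcome measures): "These measures will be obtained from both intervention and control groups at baseline and 6 months after the delivery of the intervention". There are two times and no intermediate assessment.
- **Primary outcome** (Primary outcome): "The primary outcome will be measured by the mean change in patient activation score", using the PAM-13-M.
- **Sizing** (Sample size determination): a two-tailed t test on the difference in mean change, with SD 9.70. The difference comes from a cited trial: "Therefore, the mean difference between the two groups was 3.93".
- **Hypothesis** (Hypotheses): "The primary hypothesis is that the mean score of patient activation would improve with the EMPOWER-SUSTAIN Self-Management e-Health Intervention". This sentence names no comparator.

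No section names the baseline score as a covariate or constrains the two arms to a common baseline mean.

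**The concern.** Three things follow from comparing changes over two times.

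1. **Precision.** A change score fixes the weight on the baseline at 1. Estimating that weight by regression leaves less residual variance unless the true slope is 1.
2. **Robustness.** If the intervention arm starts lower by chance, part of its later rise is regression to the mean. A change score counts that as gain. Randomisation is in blocks of four with no stratification on baseline activation described, so such imbalance is left to chance. The Study setting section says the pilot should give safe assumptions about effect size for the definitive trial, so a noisier estimate matters here.
3. **Interpretation.** Within-arm comparisons are listed on the same footing as between-arm ones. A rise within the intervention arm does not show an intervention effect, because usual-care patients may rise too.

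**Working it through.** **Inputs** (Sample size determination unless noted)
- Cited trial, intervention arm: 65.33 to 71.30, change 5.97, SD 9.70.
- Cited trial, control arm: "In the control group, the mean patient activation score at baseline was 66.89", final mean 68.93, change 2.04, SD 10.01.
- Difference 3.93, SD 9.70, two-sided alpha 0.05, power 80%, 97 evaluable and 116 recruited per arm, 20% drop-out.
- rho, the correlation between baseline and 6-month PAM-13-M: not in the documents, so assumed over a range.

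**Step 1: the plan's own figure.** By the normal approximation, n = 2 × [9.70 × (1.960 + 0.842) / 3.93]² = 95.6, so 96. By the noncentral t distribution, power is 79.8% at 96 and 80.2% at 97. The stated 97 per group is reproduced.

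**Step 2: equivalence.** On one simulated data set with complete pairs (97 per arm), the group-by-time F was 12.3225 and the squared t on change was 12.3225. A random-intercept mixed model with separate baseline means gave the same estimate and the same squared statistic.

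**Step 3: precision.** Let s be the common SD at both times.
- Change score: variance 2s²(1 − rho).
- Baseline-adjusted: variance s²(1 − rho²).
- Ratio: (1 + rho)/2, which is below 1 whenever rho is below 1.

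Holding the change SD at 9.70, the adjusted SD is 9.70 × √[(1 + rho)/2]. With 116 × 0.8 = 92.8 per arm and a difference of 3.93, noncentral t gives:

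| Analysis | Variance ratio | SD | Power |
|---|---|---|---|
| Change score | 1 | 9.70 | 78.4% |
| Adjusted, rho 0.5 | 0.75 | 8.40 | 88.7% |
| Adjusted, rho 0.7 | 0.85 | 8.94 | 84.6% |
| Adjusted, rho 0.8 | 0.90 | 9.20 | 82.5% |
| Adjusted, rho 0.9 | 0.95 | 9.45 | 80.4% |

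These figures allow for no clustering by physician. In 4,000 simulated trials per rho at 97 per arm, power was 79.8% / 80.0% / 79.6% for change scores and 93.0% / 89.1% / 85.2% for adjustment at rho 0.3 / 0.5 / 0.7. Both estimates averaged about 3.92 against a true 3.93, so neither is biased.

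**Step 4: baseline imbalance.** Under the same model, the change-score estimate has correlation −√[(1 − rho)/2] with the baseline difference between arms: −0.59, −0.50 and −0.39 at rho 0.3, 0.5 and 0.7. The simulations gave −0.57, −0.49 and −0.37. The adjusted estimate had correlations of 0.01 to 0.03.

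**Step 5: the cited trial as an example.**
- Baseline difference: 65.33 − 66.89 = −1.56.
- Final difference: 71.30 − 68.93 = 2.37.
- Difference in change: 2.37 + 1.56 = 3.93.
- Adjusted difference: 2.37 + b × 1.56 for slope b, which is 3.15 at b = 0.5 and 3.62 at b = 0.8.

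**Step 6: within-arm tests.** Take the cited control change of 2.04 with SD 10.01. At 97 per arm, 2.04 / (10.01/√97) = 2.01, so a within-control test would be significant about 51% of the time with no intervention.

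**The case against.** The strongest reply is that nothing here is wrong. Outcome, sample size and analysis all target the difference in mean change and agree with one another, and randomisation makes that comparison unbiased. An article may also leave covariates to an analysis plan. The first part stands: this is a loss of precision and robustness, not an error of validity. The second does not remove the point, because the article itself names the model and makes mean change its target.

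Several stronger readings are tempting, and the documents do not support them.

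- *The plan will test the group main effect, or leaves the decisive term open.* The main effect is never proposed. Comparing mean changes between groups over two times is the group-by-time contrast.
- *The investigators mean to claim effectiveness from improvement in the intervention arm alone.* The hypothesis sentence read by itself might suggest this. The objective at the end of the Background, the Trial design section and the sample size all set the intervention against usual care. What remains is that the within-arm comparisons carry no label saying they are descriptive.
- *1.56 of the 3.93 is spurious.* That would take the raw final difference of 2.37 as the effect, which means a slope of 0. For slopes of 0.5 to 0.8, imbalance accounts for about 0.3 to 0.8 points. The slope is assumed, and the example concerns another trial.
- *Adjustment is certain to make good the drop-out shortfall.* The power figures ignore clustering. As an illustration, 92.8 patients over five intervention physicians is 18.6 each. An assumed intracluster correlation of 0.01 to 0.05 then gives a design effect of 1 + 17.6 × ICC, about 1.2 to 1.9, which could absorb the gain.
- *The planned analysis is always identical to a t test.* With missing 6-month scores a likelihood-based mixed model departs slightly from it, and a common-baseline model would already behave like the adjusted analysis. The article specifies no such constraint.

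**Conclusion.** The point holds as one of efficiency, robustness and labelling. The planned between-arm comparison is sound but gives up precision that the planned data can supply. Under equal SDs at both times, the adjusted variance is lower by 25% at rho 0.5 and by 5% at rho 0.9, and the gain vanishes as rho approaches 1. Without clustering, power moves from just below the 80% target to just above it at rho 0.9 and to nearly 89% at rho 0.5. Adjustment also makes the effect estimate essentially uncorrelated with chance baseline imbalance, which matters in a pilot meant to inform a definitive trial. The within-arm comparisons need a label rather than removal. This merits a change before analysis, but the trial's validity does not depend on it.

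**What to change.** In the Effectiveness analysis section, or in an analysis plan finalised before outcome data are seen:

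1. State that the primary estimate is the between-arm difference in 6-month PAM-13-M adjusted for baseline PAM-13-M, with a 95% confidence interval. A mixed model with a common baseline mean for both arms is an equivalent choice, and it keeps patients who have only one of the two scores.
2. Use the same approach for the other continuous outcomes, each adjusted for its own baseline.
3. State that within-arm changes are descriptive and that potential effectiveness is judged only on the adjusted between-arm difference.
4. Report the observed baseline-to-6-month correlation and the adjusted residual SD, so that the definitive trial need not assume them.

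The cost is analysis wording. Baseline scores are already planned to be collected in both arms, so no extra visit, measurement or patient is needed. The Trial status section shows that recruitment had not started at publication.

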### Feasibility outcomes

Process evaluation to assess the integrity of the randomised controlled trial protocol will be conducted. These include recruitment rate, methods of randomisation, retention rate, appropriateness of the primary and secondary outcome measures, sample size calculation, whether the intervention could be delivered as intended, and methods of statistical analysis to evaluate the potential effectiveness. Qualitative studies to explore facilitators and barriers in delivering the intervention among PCPs and using the intervention among patients will also be conducted. However, detailed methods for the qualitative studies are beyond the scope of this paper.

### Data monitoring

Data monitoring will be done by the EMPOWER-SUSTAIN investigators. Data on any adverse event or unintended effect of trial intervention or trial conduct will be collected, assessed, reported and managed by the investigators. An external data monitoring committee is not needed, because the intervention does not involve a new pharmacological agent or regulated device.

## Discussion

To the best of our knowledge, the EMPOWER-SUSTAIN project is the first self-management e-health intervention designed for patients with MetS in the Malaysian primary care setting. The pilot randomised controlled trial will be conducted to evaluate the feasibility and potential effectiveness of the EMPOWER-SUSTAIN intervention, including recruitment rate, methods of randomisation, retention rate, selection of primary and secondary outcome measures, sample size calculation, whether the intervention could be delivered as intended, and methods of statistical analysis to evaluate the potential effectiveness [44, 45]. All of these aspects will be useful for further exploration in a larger definitive trial.

The EMPOWER-SUSTAIN Self-Management e-Health Intervention is expected to yield important new evidence on the potential improvements of patient activation and self-management behaviours among patients with MetS in a developing country. It is hypothesised that patients’ activation, WC, BMI, blood pressure, PA level, eating behaviour, perception and experience of receiving chronic disease care, patient–physician satisfaction, and perceived absolute 10-year CVD risk would improve with the EMPOWER-SUSTAIN Self-Management e-Health Intervention.

The EMPOWER-SUSTAIN intervention is a complex, multifaceted chronic disease management strategy based on three CCM elements (i.e., delivery system design, self-management support and decision support). It consists of training the PCPs, nurse, and patients to use the EMPOWER-SUSTAIN web-based self-management mobile app, strengthening patient–physician relationship, and reinforcing the use of relevant CPG for management and prescribing. This intervention is developed on the basis of MRC recommendations, guided by the best available evidence and appropriate framework [46, 47].

It is well established that the CCM is one of the best-known models to transform chronic disease care [11]. The EMPOWER-SUSTAIN intervention focuses on linking informed, activated patients with proactive and prepared practice team (i.e., PCPs and nurse) [11, 86]. The self-management mobile app is developed as a tool for health care providers to support and engage patients so that they are empowered with knowledge, skills and confidence to take independent actions to manage their own health [11, 12].

Development of an e-health intervention to support patients’ self-management requires careful planning and the use of theory-based strategies to increase the probability of effectiveness, programme adoption and implementation [34–37]. Therefore, the EMPOWER-SUSTAIN self-management mobile app is developed using the persuasive technology theory [39]. It consists of evidence-based content presented in a user-friendly interface, with incorporation of interactivity, reward system, problem-solving assistance, patient–physician collaboration, and regular reinforcement to ensure sustainability [34–37, 49, 87–89]. It is designed to aid and motivate people to adopt a positive attitude and behaviour change through persuasion and social influence [39].

To ensure effective patient–physician collaboration, PCPs will be trained prior to the delivery of intervention. In the EMPOWER-SUSTAIN Workshop, PCPs and a nurse will be trained on the basis of SDT, an evidence-based framework of human motivation and personality theory which supports the individual’s experience of autonomy, competence, relatedness and engagement for activities [65]. It is useful for them to understand that individuals’ behaviour change can be influenced by the role of a health care provider [65]. They will also be trained on MI techniques and health-coaching skills to facilitate patients’ autonomous self-regulation to enhance their behaviour change by enabling patients to develop individualised action plans [65–68].

PCPs assisted by a nurse will then train individual patients on how to use the EMPOWER-SUSTAIN self-management mobile app based on the KTA Framework [69]. This framework is chosen because it is context-focused, enables knowledge-producer and knowledge-user collaboration, and emphasises sustainability [69]. The KTA Framework incorporates the need to adapt the knowledge to fit with individual context. This framework is particularly useful for emphasising the collaboration between knowledge producers and knowledge users [69]. Sustainable knowledge use is essential, given the chronic nature of MetS and the associated CV risk factors. Apart from the KTA Framework, the PCPs and nurse will also apply the MI techniques and health-coaching skills to influence behaviour change in these patients. A systematic review on the effectiveness of MI in primary care has reported positive outcomes of this intervention on health behaviour change [50].

Another essential component of the CCM is clinical decision support [11]. Clinical management should be tailored to individual patients’ needs, guided by evidence-based decision support tool (i.e., the CPG) [11]. Therefore, PCPs will be trained to use the relevant evidence-based CPG to support management and prescribing for patients with MetS. This would empower PCPs to improve their clinical management [90].

